### Outcome measures

All the participants were assessed and measured for the included outcomes at the outpatient clinic before the procedure, and in 2, 4, 8, 12, and 24 weeks after ACLR by two assessors. Outcome measures were conducted before face-to-face guidance for exercise methods at every visit in the outpatient clinic.

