### Primary outcome

The primary outcome was the percentage of patients who achieve a satisfactory active ROM at the 12 weeks following the ACLR. In the first 3 months after ACLR, the achievement of acceptable knee active extension and flexion was regarded as what matters most for a successful recovery. A good knee active ROM could guarantee an expectedly continue improvement [6]. The satisfactory active ROM was also collected at 2, 4, 8, and 24 weeks after ACLR.

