### Secondary outcomes

The secondary outcomes were active and passive ROM, pain, muscle strength, and function results.

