### Statistical analysis

All the data collect and analyses will be performed by two independent researchers who were blinded to the group allocation in SPSS 22.0 (IBM, USA) software. Participants who dropout or lost to follow-up would be excluded. Demographic characteristics and follow-up outcome data would be included in the analysis. The independent sample t-test or nonparametric analysis would be used to evaluate continuous variables, while chi-square test or Fisher’s exact test evaluate the categorical variables, and repeated-measures ANOVA evaluate the repeated measures data.Bilateral test was utilized in all the analysis and *P* < 0.05 was regarded as statistically significant.

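### The named tests for the continuous secondary outcomes leave the preoperative value unused as a covariate, and classical repeated-measures ANOVA keeps only participants seen at every visit

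*Protocol article*

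**What the plan says.** The Statistical analysis section of the protocol article assigns tests by type of data. For continuous variables: "The independent sample t-test or nonparametric analysis would be used to evaluate continuous variables". Categorical variables get a chi-square or Fisher's exact test. For the rest: "repeated-measures ANOVA evaluate the repeated measures data". No covariate, contrast or key visit is named for any of these. The same section says "Participants who dropout or lost to follow-up would be excluded", and the analyses are to be run "in SPSS 22.0 (IBM, USA) software".

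The Outcome measures section says that all participants are assessed on the included outcomes "before the procedure, and in 2, 4, 8, 12, and 24 weeks after ACLR by two assessors", which makes one preoperative and five postoperative assessments. The Pain section speaks of postoperative pain, so a preoperative pain score rests on this general statement.

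The outcomes concerned are listed under Secondary outcomes: "The secondary outcomes were active and passive ROM, pain, muscle strength, and function results". Week 12 is fixed only under Primary outcome: "The primary outcome was the percentage of patients who achieve a satisfactory active ROM at the 12 weeks following the ACLR".

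**The concern.** The preoperative measurement is collected but does not enter any between-group comparison as a covariate. Where baseline predicts follow-up, an unadjusted test has a larger standard error than it needs, and a chance imbalance between the arms stays in the estimate.

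Classical repeated-measures ANOVA works on complete rows. A participant who misses one clinic visit contributes nothing, even with the other visits on file. The article does not state this deletion; it follows from the method named. The article itself plans for 20% attrition. Participants are not blinded and only one arm can contact therapists online, so missed visits could differ between arms. A complete-case analysis then needs a stronger assumption about why data are missing than a likelihood-based model that uses every observed visit.

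These outcomes are secondary, but they carry most of the stated hypothesis, which is superiority in range of motion, pain, muscle strength and overall function.

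**Working it through.** **The plan's own figure.** The Sample size determination section gives 44 per group and 110 in total, from 95%, a 20-point difference, 80% power and α = 0.05. Reading this as 95% against 75% (the 75% is inferred), the exact power of a two-sided chi-square test without continuity correction is 0.794 at 43 and 0.804 at 44 per group. Then 44 / 0.80 = 55 per group, or 110. So 44 and 110 reproduce. They rest on the binary primary outcome, and nothing below changes them.

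**Inputs for the continuous outcomes**

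- From the article: 44 evaluable per arm, 110 randomised, two-sided α = 0.05, five postoperative visits.
- Assumed, because the article gives no such figures: a true difference of 0.5 SD at a single visit; baseline-to-follow-up correlation r = 0.3, 0.5 or 0.7; independent missingness of 3%, 5% or 10% per postoperative visit.

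**1. Baseline as a covariate.** Adjustment multiplies the residual variance by 1 − r², so the standardised effect becomes 0.5 / √(1 − r²). The noncentrality of the two-sample t-test is that effect × √(44/2), that is, × 4.690.

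| Analysis | 1 − r² | Effect (SD) | Noncentrality | Power |
|---|---|---|---|---|
| Unadjusted | 1.00 | 0.500 | 2.345 | 64% |
| Adjusted, r = 0.3 | 0.91 | 0.524 | 2.458 | 68% |
| Adjusted, r = 0.5 | 0.75 | 0.577 | 2.708 | 76% |
| Adjusted, r = 0.7 | 0.51 | 0.700 | 3.284 | 90% |

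At r = 0.5 the gain equals that from 1 / 0.75 = 1.33 times as many participants.

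**2. Complete rows in the ANOVA.** The share with all five postoperative visits is (1 − m)⁵.

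| Missed per visit, m | (1 − m)⁵ | Remaining of 110 |
|---|---|---|
| 3% | 0.859 | about 94 |
| 5% | 0.774 | about 85 |
| 10% | 0.590 | about 65 |

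The plan expects 2 × 44 = 88 evaluable participants.

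**3. Is the ANOVA always the weaker test?** Take a constant 0.5 SD effect at all five postoperative visits, equal correlation r between visits, and the preoperative value entered as one of six time levels. The averaged difference is 0.5 × 5/6 = 0.417 SD, and the SD of a participant's mean is √((1 + 5r)/6) = 0.645, 0.764 or 0.866. Power of the group main effect at 44 per arm is then 85%, 72% or 61%. At r = 0.3 and 0.5 this exceeds the 64% of a single-visit t-test, and at r = 0.3 it also exceeds the 68% of a single-visit adjusted analysis. Averaging visits lowers the variance and can more than repay the dilution. So there is no general statement that the ANOVA loses power; it depends on how the effect runs over time.

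**The case against.** The strongest reply is that these are secondary outcomes, that randomisation keeps unadjusted tests valid, and that covariates and missed-visit rules are commonly left to an SAP. The first two parts stand and limit the point. The third does not remove it: the article names its methods, and the point is that better ones are available for the same data.

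A reader might infer several stronger things that the article does not support.

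- *That the t-tests also drop anyone with a missed visit.* A t-test at one visit loses only those absent at that visit. The stated exclusion of dropouts is a separate rule.
- *That the plan fails to target week 12.* Week 12 is declared only for the primary outcome. A t-test could be run then, and a trajectory comparison fits the Discussion's expectation of faster recovery.
- *That two tests compete for the same data.* The t-tests may be meant only for single-occasion variables such as age, with the ANOVA for repeated outcomes. The wording allows both readings.
- *That entering baseline as a time level must weaken the ANOVA.* The article does not say it will be entered so, and step 3 of the working shows that the 5/6 dilution is not the whole account.
- *That the ANOVA must assume the same correlation between every pair of visits.* Sphericity is a weaker condition than that, it can be corrected for, and the between-group main effect does not require it.
- *That leaving out baseline biases the result.* It does not. The bias risk comes from excluding participants.

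The reply is also right that replacing every test with one linear model would leave bounded scales such as VAS and Tegner without the nonparametric option that the article now gives them. The fix must keep one.

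**Conclusion.** The point holds as an improvement to the analysis of the continuous secondary outcomes. The named methods do not use the preoperative value as a covariate, and the classical repeated-measures ANOVA discards partly observed participants.

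The precision gain runs from 4 percentage points of power at r = 0.3 (64% to 68%) to 26 points at r = 0.7 (64% to 90%), for an assumed 0.5 SD effect at 44 per arm. If preoperative values after an acute rupture predict recovery poorly, the gain lies at the lower end. The loss of participants from the ANOVA runs from about 16 to about 45 of 110 over 3% to 10% missed per visit. At 5%, the 85 remaining are close to the 88 planned, so on that assumption the loss is modest. Missed visits that cluster in the same people would leave more complete rows than independence implies.

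All these sizes rest on assumed correlations, effect and missingness. The primary analysis, the sample size and the validity of the randomised comparison at baseline are not in question.

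**What to change.** For each continuous secondary outcome, replace the between-group t-test and the repeated-measures ANOVA with one linear mixed model on all observed postoperative visits from all randomised participants. Its terms are group, visit, group-by-visit and the preoperative value as covariate. An unstructured covariance across the five visits avoids relying on sphericity.

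Report the adjusted group difference with its 95% confidence interval at each visit, and name one visit in advance as the main one. Week 12 would match the primary outcome, but the choice is the investigators'. Keep a nonparametric or ordinal sensitivity analysis for bounded or skewed scales such as VAS and Tegner. State that the exclusion of participants who drop out does not apply to this model, so that their observed visits are used.

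The cost is a change of wording, best fixed before any unblinded analysis. SPSS 22 can fit the model, and no new data or participants are needed.

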### Ethics and dissemination

The study was approved by the ethics committee of West China Hospital of Sichuan University (approval number 2023−1929, Dec 2023). Before participate recruitment, the study was registered in the ClinicalTrials.gov (registration number NCT06232824, Jan 2024). This study complies with the Declaration of Helsinki and written informed consent would obtained from each participant prior to enrolment. Any important protocol amendments will be reported to the ethics committees and ClinicalTrials.gov. The study findings would be disseminated in scientific forums, peer-reviewed publications, and international conferences. Outcomes would be propagated regardless of the magnitude or direction of the impact.

## Discussion

The results of the study may demonstrate that multicomponent supervised tele-rehabilitation could accelerate the recovery over traditional home-based self-rehabilitation following ACLR. Multicomponent supervised tele-rehabilitation is expected to relieve pain, improve ROM, muscle strength, and function.

The health care system has undergone significant changes due to the profound effects of the COVID-19 pandemic [27]. The inaccessibility of face-to-face post-operative rehabilitation during this period has prompted the swift emergence of contactless rehabilitation methods [28].Supervised rehabilitation under the guidance of a licensed therapist might prove more efficacious than engaging in unsupervised exercise [29]. A retrospective cohort study found that telerehabilitation after ACLR seems to provide a superior short-term outcome compared to hospital-based rehabilitation during the COVID-19 pandemic [30].

The purpose of ACLR is to maximize the stability and functional capacity of the knee joint, and therefore facilitate return to sports [4]. However, approximately 50% of individuals with injuries will manifest symptomatic osteoarthritis within a decade, irrespective of whether they undergo operative or non-operative treatment [31]. Despite the perceived benefits of exercise therapy for ACLR, there is a lack of consensus on its optimal components [32]. Most trials conducted after ACL injury lack individualized interventions, employing the same program for all patients, and fail to adequately document exercise frequency, intensity, volume, and progression [33]. Therefore, implementing personalized and supervised ACLR rehabilitation is crucial. Technological advancements and digital solutions may be considered promising tools for implementing a comprehensive rehabilitation approach for patients after ACLR. Recent studies have also confirmed the potential advantages of remote rehabilitation in post-ACLR management [34]. In the treatment of ACL injuries, rehabilitation assumes a pivotal role, yet its implementation prior to or following ACLR have not be standardized in a uniform manner due to the intricate nature of individual cases in the context of modern evidence [35–42].Unlike many tele-rehabilitation programs that primarily focus on post-discharge follow-up, weconducted a multi-component supervised tele-rehabilitation with comprehensive services. We offer education, visually guided user interface assistance for functional exercises, interactive real-time communication, and evaluations during both active and passive follow-up periods, which offering additional evidence supporting a advanced tele-rehabilitation after ACLR.

Figure 1. The flowchart of the whole study.

Figure 2. The interface of the HJT software. **A**: The main page of the HJT software, the timeline of the experiment was also presented in the main page. **B**: The page of the software displays the preoperative education. **C-D**: The page of the software displays the part of postoperative rehabilitation. **E**: The page of the software displays the interactive real-time communication.

**Fig. 2 Fig2:**
[figure not shown]
The interface of the HJT software. **A**: The main page of the HJT software, the timeline of the experiment was also presented in the main page. **B**: The page of the software displays the preoperative education. **C-D**: The page of the software displays the part of postoperative rehabilitation. **E**: The page of the software displays the interactive real-time communication

## Data Availability

No datasets were generated or analysed during the current study.
